### Lung and IVC ultrasound protocol

All the patients will undergo lung and IVC ultrasound using a Philips Lumify hand-held ultrasound device. The ultrasound will be performed by physicians specialised in lung and cardiovascular ultrasound and will be quantified off-line in an echocardiography laboratory made up of three independent physicians who will be blinded to the study group, patient information and interpretation of the other expert reviewer.

The results of the ultrasound will be reported in three categories (figure 3):

Group A—no congestion or mild residual congestion.

Group B—signs of right-sided or left-sided congestion or both.

Group C—severe signs of right-sided or left-sided congestion and worse prognosis.^2 25 32 33 37^ The cut-off value of ≥5 B-lines was chosen as sign of persistent congestion, since it was found to be a risk factor for the occurrence of the primary endpoint of rehospitalisation, unexpected visit for worsening HF or death at 6-month follow-up.^28^ The presence of >30 B-lines is considered severe congestion as it proved to be a strong predictor of hospitalisation for HF or mortality at 90 days (HR 5.66, 95% CI 1.74 to 18.39).^25^

**Figure 3 F3:**
[figure not shown]
CAVAL US groups. IVC, inferior vena cava; LUS, lung ultrasound.

### Technique and quantification

IVC assessment: the IVC is assessed as recommended in the current echocardiography guidelines. Cardiac transducer of 3–7 MHz, in the cardiac preset, depth of 10 cm. The patient is kept in a supine position with the least elevation of the upper body possible (<20°) The IVC is scanned in its long axis from the subcostal view. The measurement of the IVC diameter is performed just proximal (1.5 cm) to the entrance of the hepatic veins at end expiration (IVCmax) and at inspiration (IVCmin). The IVC collapsibility index is derived from these parameters as percentage collapse of the maximal IVC diameter as follows: (IVCmax−IVCmin)/IVCmax×100. An IVC diameter <21 cm with collapsibility >50% is normal, while IVC is dilated when its diameter is >21 mm and collapsibility <50%.^38^

LUS: the procedure will be performed using a portable ultrasound device. The eight-zone method will be used to evaluate eight chest zones (four zones in each hemithorax) according to international recommendations.^39^ Dividing lines include the sternum medially, the anterior axillary line dividing medial and lateral zones, and the posterior axillary line laterally. The third intercostal space divides the superior and inferior zones.

The probe will be positioned perpendicular to the ribs, with a scanning depth of 16 cm and the patient in semirecumbent position. Gain will be adjusted to each patient so that the shadows of the ribs are black and the pleural line with lung sliding is seen clearly. A 6-second video clip of each zone will be recorded. B-lines are defined as comet-tail, vertical artefacts arising from the pleural line, moving in synchrony with lung sliding (when present), well defined and laser like, extending to the bottom of the screen without fading. The highest number of B-lines (vertical lines arising from the pleural line) visualised in a single intercostal space will be recorded for each zone. The white lung pattern is counted as 10 B-lines, and fused B-lines are counted as the percentage of the rib space filled with confluent B-lines divided by 10 and added to any other B-lines noted in the space at that instant.^39^ A positive region is defined by the presence of three or more B-lines in a longitudinal plane between two ribs.^21^ The presence of pleural effusion will also be evaluated, and its size will be categorised offline on 6-second clips using a semiquantitative score called pleural effusion (PEF) score, ranging from 0 to 4 points for each hemithorax (box 2) with a total score ranging from 0 to 8. Significant pleural effusion will be defined as a PEF score of 5–8 and non-significant pleural effusion when PEF score is less than 5.^40^

Box 2Definition of the pleural effusion (PEF) score for each hemithorax.^40^
4—pleural effusion occupies more than 50% of the basal pleural cavity visible in the standardised imaging plane.3—clear separation between diaphragm and lung base at any point during the respiratory cycle.2—pleural effusion extends over the costophrenic angle without a clear separation of the lung base from the diaphragm.1—pleural effusion is only visible in the costophrenic angle.0—pleural effusion is not visible.The box has been reproduced with permission from Lindner *et al*.^40^

Before the trial began, cardiologists and ultrasound specialists attended a workshop for specific technical training to standardise the way the examination is conducted, interpreted and reported. The workshop lasted 24 hours (18 hours of theory and 6 hours of practice).

### Study endpoints and follow-up

The primary endpoint is the presence of subclinical congestion at discharge, defined as the presence of more than five B-lines and/or an increase in the diameter of the IVC, with and without collapsibility.

The secondary endpoint is the composite of readmission for HF, unplanned visit for worsening HF or death at 90 days. Additionally, we will assess other secondary endpoints such as the variation of pro-B-type natriuretic peptide at discharge, length of hospital stay, total number of HF hospital admissions and diuretic dose at 90 days (box 3). AHF hospitalisation was defined as unscheduled urgent hospital visit and hospital stay >24 hours, requiring intravenous HF therapies (diuretics, vasodilators, inotropes). Urgent AHF visits were defined as unscheduled visit to the emergency department resulting in increased dose of oral/intravenous therapy, stay <24 hours.

Box 3Secondary endpointsComposite outcome: readmission for heart failure (HF), unplanned visit for worsening HF or death at 90 days.All-cause mortality at 90 days.Duration of index hospital stay.Reduced total readmissions (first and recurrent) for HF at 90 days.Increased requirement for diuretics: patients who required a higher dose of furosemide compared with the dose indicated on hospital discharge.Pro-B-type natriuretic peptide (NT-proBNP) at discharge.% change of NT-proBNP (admission–discharge).

The safety endpoints during the index hospitalisation include:

Hypotension (systolic blood pressure <90 mm Hg).Requirement of vasoactive drugs (inotropic/pressor agents).Worsening renal function leading to a creatinine increase of ≥50% or >0.3 mg/dL on any of the blood tests performed during the index hospitalisation.Hypokalaemia <3.5 mmol/L or hyperkalaemia >5 mmol/L.

At 90 days after randomisation, two independent physicians, blinded to the assigned group, will adjudicate events by telephone contact. In case of disagreement, a third independent physician will evaluate the case.

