## Introduction

Despite the important therapeutic advances, the prevalence of heart failure (HF) is increasing^1^ and is still a major healthcare issue due to its high morbidity and mortality.^2^ Approximately 25%–30% of patients hospitalised for acute HF (AHF) are readmitted within 90 days after discharge, and 50% within 6 months.^3–5^ The post-discharge period, known as the ‘vulnerable phase’,^6^ is associated with high risk of unfavourable outcomes.^7 8^ Readmission of these patients does not only increase costs but is also a signal that current approaches to HF management are not optimal. In fact, the greatest threat to patients with AHF is the risk of readmission due to persistent congestion.^9–11^

Remaining clinical congestion at discharge is a strong predictor of mortality risk^12 13^; therefore, its assessment prior to hospital discharge remains a crucial opportunity to treat patients who have not yet reached the optimal euvolemia. However, the optimal evaluation of decongestion in AHF is not clearly defined in the guidelines,^14 15^ which may be partly explained by the lack of effective measurement methods.^10 16^ Monitoring patient fluid status is a dynamic and challenging process with a broad spectrum of clinical presentations and parameters to consider. Physicians are faced with the daily task of making critical decisions with a handful of tools and a significant gap in evidence as above mentioned.^17^

Evaluation and monitoring of fluid excess status in patients admitted for acute decompensated HF are currently based on clinical history, physical examination, chest X-ray and natriuretic peptides.^10^ However, all these elements have an inherent substantial interobserver variability and may be non-specific,^18 19^ and plasma levels of biomarkers have a limited capacity to assess quantitatively the extent of fluid retention.^20^

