**Figure 2 F2:**
[figure not shown]
Therapeutic algorithm. Adapted from: Mullens *et al*
35 and Hollenberg *et al*.^36^ BP, blood pressure; CAVAL US, inferior vena cava and lung ultrasound; IV, intravenous; LCOS, low cardiac output syndrome; UO, urinary output.

All the patients will undergo lung and IVC ultrasound, independently of the group assigned during randomisation. Furthermore, an echocardiogram will be performed within 48 hours from admission according to the recommendations,^15^ as part of our standard of care.

A checklist will be made prior to hospital discharge to assess compliance with guideline-based treatment, vaccination, counselling and medical appointment after discharge. All patients will receive education by an HF nurse, who will provide educational material and drug treatment indications in a written grid.

Patients will be randomised into two arms and will be blinded to the assigned arm:

Control group: the treating medical team will be blinded to the lung and IVC ultrasound results. Patients will receive the standard of care of our centre and titration of diuretics will be based on standard practices (physical examination, symptoms and results of laboratory tests). The therapeutic goal (see figure 2) will be to discharge patients with relief of signs and symptoms of congestive HF, without ECG changes or abnormal laboratory findings that contraindicate hospital discharge. Circulating biomarkers of congestion are not part of the standard of care.Intervention group: the treating medical team will be unblinded to the lung and IVC ultrasound results. Patients will receive treatment for decongestion according to the results of the intervention plus the standard care (figure 2). The therapeutic objectives will be similar to the control group, with relief of the signs and symptoms of HF and additionally without congestion or mild residual congestion in the ultrasound test. At the discretion of the treating physician, the patient may be discharged when he or she shows mild to moderate signs of congestion in improvement with oral diuretics for more than 24 hours with adequate diuretic response.

Both groups will be scheduled to follow-up visits in our ambulatory clinic 7–10 days after discharge, and at least once per month.

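### The two heart failure event definitions are not exhaustive: a stay over 24 hours with oral intensification only, or of exactly 24 hours, counts as no event, while a shorter visit with the same treatment counts

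*Protocol article*

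**What the plan says.** All definitions are in the protocol article under Study endpoints and follow-up.

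- Hospitalisation: "AHF hospitalisation was defined as unscheduled urgent hospital visit and hospital stay >24 hours, requiring intravenous HF therapies".
- Urgent visit: "Urgent AHF visits were defined as unscheduled visit to the emergency department resulting in increased dose of oral/intravenous therapy, stay <24 hours".
- Where the events are used: "The secondary endpoint is the composite of readmission for HF, unplanned visit for worsening HF or death at 90 days". Box 3 adds a recurrent-event endpoint: "Reduced total readmissions (first and recurrent) for HF at 90 days".
- Who classifies: "two independent physicians, blinded to the assigned group, will adjudicate events by telephone contact", with a third physician if the two disagree.

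The composite and Box 3 name their components in other words than the two defined terms. The text does not say that they are the same events, although that is the natural reading.

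Box 1 (eligibility) takes a hospital stay of at least 24 hours for decompensated HF as the qualifying admission, so exactly 24 hours is a hospitalisation at entry. The Statistical analysis plan section analyses time to first event.

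**The concern.** The hospitalisation definition joins two conditions, length of stay and intravenous treatment. Such a rule may well be deliberate. It then needs a second category that takes in the episodes failing either condition. The urgent-visit category does not do so, because it is itself capped at less than 24 hours. Episodes that are too long for a visit and lack the intravenous drug for a hospitalisation have no category.

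The result runs against the evident purpose of the composite. For the same intensification of oral treatment, a short emergency visit counts and a longer stay does not. The lead secondary endpoint can thus omit the episode that, on its face, is the more serious. The count of total HF readmissions rests on the same hospitalisation definition and so shares the open 24-hour boundary.

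**Working it through.** **Step 1. Cross the two definitions.** Inputs: the stay and treatment conditions in Study endpoints and follow-up. Every row is an unscheduled emergency department or hospital presentation for worsening HF.

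| Stay | Treatment | Hospitalisation? | Urgent visit? | Counts? |
|---|---|---|---|---|
| <24 h | oral increase | no (stay) | yes | yes |
| <24 h | intravenous | no (stay) | yes | yes |
| exactly 24 h | oral increase | no (stay, no IV) | no (stay) | **no** |
| exactly 24 h | intravenous | no (stay) | no (stay) | **no** |
| >24 h | oral increase only | no (no IV) | no (stay) | **no** |
| >24 h | intravenous | yes | no (stay) | yes |

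Three cells with intensified treatment are unclassified. The first and fifth rows have the same treatment and differ only in duration; the shorter counts and the longer does not.

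**Step 2. Compare the boundary with Box 1.** Entry: at least 24 hours is a hospitalisation. Follow-up: more than 24 hours is a hospitalisation and less than 24 hours a visit. The value 24 belongs to hospitalisation at entry and to nothing at follow-up.

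**Step 3. The plan's own figure.** The article states 29 per arm for 70% v 35%, 80% power, two-sided 5%. The unpooled normal approximation reproduces it: (1.960 + 0.842)² × (0.70×0.30 + 0.35×0.65) / 0.35² = 7.85 × 0.4375 / 0.1225 = 28.03, rounded up to 29. This concerns the primary ultrasound endpoint, which does not use the HF event definitions, so the gap leaves it unchanged.

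**Step 4. Upper bound for one omitted patient.** Inputs: 29 per arm, and the Introduction's background rate: "Approximately 25%–30% of patients hospitalised for acute HF (AHF) are readmitted within 90 days after discharge".

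- Shift in an arm's event proportion: 1/29 = 3.4 percentage points.
- Expected readmissions per arm: 29 × 0.25 = 7.25 to 29 × 0.30 = 8.7.
- Relative change in that count: 1/8.7 = 11% to 1/7.25 = 14%.

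These are upper bounds. The 3.4 points apply only if the patient has no other qualifying event within 90 days; otherwise a time-to-first-event analysis still counts the patient and only the event time may move. The 11–14% uses readmissions alone as denominator, whereas the composite also counts urgent visits and deaths.

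**Step 5. Range for the whole trial.** The documents give no share for the unclassified episodes. Assume 2% to 20% of readmission-type events, with both arms at the background rate.

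- Events in 58 patients: 58 × 0.25 = 14.5 to 58 × 0.30 = 17.4.
- Omitted: 14.5 × 0.02 = 0.3 to 17.4 × 0.20 = 3.5.

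The 2–20% is an illustration, not an estimate.

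**The case against.** The strongest reply is that this is a drafting gap in a secondary endpoint of a trial that its own Introduction calls a pilot, with 90-day events to be explored. Requiring intravenous treatment for a hospitalisation may be intended, a stay of exactly 24 hours will hardly ever occur, and rules for borderline cases often sit in a full protocol or an adjudication charter. The example patient may also be caught by the Box 3 endpoint on a furosemide dose above that at discharge. Much of this stands as a limit on size. It does not remove the point: both definitions are stated outright and it is their content that leaves the gap, and capture under another endpoint does not put the episode into the composite.

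A reader might infer more than the documents support:

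- **That the composite will be wrong to a material degree.** The only possible effect is omission of some episodes, and nothing shows that they are common.
- **That the arms will be counted differently.** The treating team sees the ultrasound results in one arm only and could in principle influence length of stay. But the definitions are the same in both arms, the adjudicators are blinded and take no part in follow-up, and the text shows no difference between arms. Blinding does not, however, supply a missing category.
- **That the trial has no other measure of clinical benefit.** Box 3 also lists all-cause mortality, total HF readmissions, index length of stay and increased diuretic requirement.
- **That unscheduled clinic visits ought to count too.** The emergency department limit is explicit, and the article's clinic follow-up text concerns planned visits: "Both groups will be scheduled to follow-up visits in our ambulatory clinic 7–10 days after discharge, and at least once per month". Adding clinic visits would be a debatable design preference that brings in a softer event.

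**Conclusion.** The point holds as a defect of definition. As written, an unscheduled HF stay over 24 hours with oral intensification only, and any stay of exactly 24 hours, is neither a hospitalisation nor an urgent visit, while an emergency visit under 24 hours with the same oral increase is an event. This assumes that the composite's readmission and unplanned-visit components are the two defined events.

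The consequence is possible omission from the 90-day composite of an unknown and probably small number of episodes: at most 3.4 percentage points in an arm for each omitted patient, and about 0.3 to 3.5 events in the whole trial under the assumed shares. The primary endpoint and the 29 per arm stand, and no bias between arms is shown. It should be corrected because the correction is nearly free.

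**What to change.** Amend the endpoint definitions in three respects:

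1. Keep the intravenous requirement for an HF hospitalisation and assign the boundary to it: a stay of ≥24 hours against <24 hours, in line with Box 1.
2. Define the urgent visit as any unscheduled emergency or hospital presentation for worsening HF, with intensified oral or intravenous HF therapy, that does not meet the hospitalisation definition, whatever its duration.
3. State that the HF readmission and unplanned-visit components of the composite, and the readmissions in Box 3, are these defined events.

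With this, every treated row of the table in the working falls into exactly one category. A long stay with oral treatment only then enters the composite as an urgent visit and stays outside total HF readmissions, which respects the intravenous requirement.

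The cost is a short amendment to the definitions and the adjudication form, and slightly more episodes for the adjudicators. No patients or procedures are added.

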### Participants and eligibility

Patients admitted with AHF in a private cardiovascular centre in Buenos Aires, Argentina. Eligibility criteria for participants are described in box 1.

Box 1Eligibility criteriaInclusion criteria (all of them)Hospitalisation of 24 hours or more for decompensated heart failure (HF) defined as new onset of symptoms or worsening of previous symptoms (including orthopnoea, progression to functional class New York Heart Association III–IV, bendopnoea or fatigue) or signs of volume overload.Jugular venous distension, hepatojugular reflux, lower extremity oedema or signs of pulmonary congestion.Chest X-ray with signs suggestive of pulmonary congestion.Elevated pro-B-type natriuretic peptide levels of 450 pg/mL, 900 pg/mL and 1800 pg/mL for ages <50 years, 50–75 years and >75 years, respectively, within 24 hours of admission.^53^
^54^
Sufficient ultrasound visualisation to assess inferior vena cava and lungs.Exclusion criteria (any of them)Not willing to participate.Life expectancy of less than 6 months.Uninterpretable lung or inferior vena cava ultrasound.Transfer to another hospital before hospital discharge.Systolic blood pressure <90 mm Hg.Chronic kidney disease (creatinine clearance <30 mL/min calculated with the Modification of Diet in Renal Disease (MDRD) study equation or haemodialysis).Requirement for invasive or non-invasive ventilator support.Pregnancy.Low cardiac output syndrome/cardiogenic shock.Death during index hospitalisation.Acute coronary syndrome, myocardial revascularisation or heart valve replacement within the previous 3 months.Being on heart transplant waiting list.Cardiac resynchronisation therapy device implanted within the previous 3 months.Severe tricuspid valve regurgitation.HF secondary to causes amenable to invasive correction: cardiac surgery, percutaneous interventions or pacemaker implantation.HF secondary to significant arrhythmias (advanced atrioventricular block or sinus arrest, sustained ventricular tachycardia or any sustained arrhythmia other than atrial fibrillation causing haemodynamic instability according to the discretion of the treating physician).HF secondary to severe systemic infection.Severe psychiatric illness.Palliative care.SARS-CoV-2 infection.

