### Statistical analysis plan

According to our preliminary pilot data derived from a sample of 20 patients during the new ultrasound tool proof trial, 70% had >5 B-lines and/or dilated IVC at discharge with the usual care strategy at our hospital. Therefore, to reach a relative risk reduction of 50% (ie, 70% in usual care and 35% in the CAVAL US-guided strategy), setting a power of 80% and a two-sided type I error rate of 5%, we will need 29 patients in each arm to accomplish our hypothesis.

Analysis will be performed by intention to treat. Continuous variables will be expressed as mean and SD, or median and IQR, according to their distribution. Normality of distribution of variables will be assessed using the Kolmogorov-Smirnov test or the Shapiro-Wilk test, according to the sample size. Continuous variables will be compared using the Student’s t-test or the Mann-Whitney U test, as applicable. Categorical variables will be presented as numbers and percentages. The Χ^2^ test or Fisher’s exact test will be used to compare proportions. No imputation will be made for missing data.

The Kaplan-Meier method will be used to analyse time-to-first event data. The differences in time-to-event distributions will be evaluated using the log-rank test. Univariate HRs with associated 95% CIs will be estimated for the composite primary endpoint and secondary endpoints and derived from the Cox proportional-hazards model; however, multivariate Cox regression analysis will only be used if there are important prognostic factors or patients’ baseline characteristics exhibiting significant imbalance between the two groups established by randomisation. In all cases, the alpha error will be set at 5% to establish statistical significance. All the statistical calculations will be performed using SPSS V.24 software package.

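### NT-proBNP is tested twice without baseline adjustment, although every patient has an admission value: valid, but less precise than one log-scale ANCOVA

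*Protocol article*

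**What the plan says.** Box 3 (Study endpoints and follow-up) lists "Pro-B-type natriuretic peptide (NT-proBNP) at discharge" and, as a separate entry, the percentage "change of NT-proBNP (admission–discharge".

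The admission value is already collected. Box 1 (Participants and eligibility) requires "Elevated pro-B-type natriuretic peptide levels of 450 pg/mL, 900 pg/mL and 1800 pg/mL" by age band, measured "within 24 hours of admission".

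The Statistical analysis plan section gives one rule for all continuous outcomes. First, "Normality of distribution of variables will be assessed using the Kolmogorov-Smirnov test or the Shapiro-Wilk test, according to the sample size". Then, "Continuous variables will be compared using the Student’s t-test or the Mann-Whitney U test, as applicable". The only covariate adjustment it mentions is for time-to-event outcomes: "multivariate Cox regression analysis will only be used if there are important prognostic factors" or baseline characteristics out of balance between the arms. Nothing similar is given for continuous endpoints. The 5% significance level applies to every test.

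**The concern.** The comparison of discharge values ignores the admission value. Percent change uses it, but inefficiently: it amounts to fixing the log-scale slope on admission at 1 instead of estimating it. When the correlation is below 1 and the variances are similar, that over-corrects, so a chance admission difference between two arms of 29 still carries into the result.

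Two tests of one measurement, each at 5%, can also disagree, and the article does not say which one carries the NT-proBNP conclusion. NT-proBNP is the only biomarker endpoint. It is also a laboratory measure, whereas the primary endpoint is read by the same technique that steers treatment in the intervention arm. It is therefore worth estimating as precisely as 58 patients allow.

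**Working it through.** **The plan's own figure.** The sample size is for the binary primary endpoint: 70% versus 35%, 80% power, two-sided 5%. The unpooled formula gives (1.960 + 0.842)² × (0.70×0.30 + 0.35×0.65) / 0.35² = 7.849 × 0.4375 / 0.1225 = 28.03, rounded up to 29 per arm. This reproduces the stated number. The article gives no SD, correlation or power for NT-proBNP, so the inputs below are assumptions.

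**Relative variance.** Take log NT-proBNP with equal variance at admission and discharge, and correlation r. The variance of the arm difference, relative to the discharge value alone, is:
- discharge value: 1
- log change: 2(1 − r)
- ANCOVA: 1 − r²

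So discharge/ANCOVA = 1/(1 − r²), and change/ANCOVA = 2(1 − r)/(1 − r²) = 2/(1 + r). Multiplying each ratio by 29 gives the patients per arm that the simpler analysis would need to match ANCOVA at 29.

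| r | discharge / ANCOVA | per arm | log change / ANCOVA | per arm |
|---|---|---|---|---|
| 0.4 | 1.19 | 34.5 | 1.43 | 41.4 |
| 0.5 | 1.33 | 38.7 | 1.33 | 38.7 |
| 0.6 | 1.56 | 45.3 | 1.25 | 36.3 |
| 0.7 | 1.96 | 56.9 | 1.18 | 34.1 |
| 0.8 | 2.78 | 80.6 | 1.11 | 32.2 |

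**Small-sample cost.** Estimating the slope inflates the ANCOVA variance by about 1 + 1/(2×29 − 4) = 1.019. With that included, ANCOVA beats the discharge value when r exceeds about 0.14, and beats log change when r is below about 0.96.

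**The tests as planned.** These ratios describe log-scale analyses, whereas the plan tests raw values or ranks. The planned rule was therefore simulated: lognormal data, 29 per arm, Shapiro-Wilk in each arm, then t-test or Mann-Whitney. The assumed geometric mean ratio is 0.6 and the log SD 1.0, with 3000 runs per row. The ANCOVA has arm and log admission only.

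| r | planned discharge test | planned % change test | ANCOVA | gain over % change (points) |
|---|---|---|---|---|
| 0.5 | 46.8% | 47.7% | 60.0% | 12.3 |
| 0.6 | 44.7% | 54.0% | 66.1% | 12.1 |
| 0.7 | 45.9% | 67.0% | 75.7% | 8.7 |
| 0.8 | 46.2% | 84.2% | 88.9% | 4.7 |

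The simulation error on each power figure is at most √(0.25/3000), about 0.9 points, so the gain over percent change is best read as about 5 to 13 points. With no true effect (r = 0.6), the rejection rate was 4.3% for the planned discharge test, 4.4% for the planned percent-change test and 4.3% for ANCOVA.

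**Two tests of one measurement.** In a separate set of 2000 runs with r from 0.4 to 0.8, the two planned tests disagreed on significance in 31% to 46% of trials under the assumed effect. With no effect, at least one was significant in 7% to 9%.

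**The case against.** A reader might infer that skewness undermines the planned analysis, since percent change is bounded below at −100% and unbounded above. The article does not support that. Skewed data go to the Mann-Whitney test. Percent change is a monotone transform of log change, so that test gives the same p-value on either scale, and the same holds for raw and log discharge values.

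A reader might also infer that the preliminary normality test makes the estimand drift between means and ranks. In principle it does. But with simulated lognormal data (log SD 0.7 to 1.0, r 0.4 to 0.8), Mann-Whitney was chosen in 99% to 100% of runs for the discharge value and 86% to 100% for percent change, and type I error stayed near or below 5%. The planned tests are valid.

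Other objections stand in part:
- Percent change already uses the admission value, so the largest gains, those against the discharge value alone, overstate what the plan as a whole loses.
- Discharge level and relative change answer different descriptive questions, and listing both is no error in itself.
- The eligibility thresholds cut off low admission values, which may lower both the admission variance and r, so the equal-variance formula is only a guide.
- The trial is called a pilot and makes no power claim for NT-proBNP.
- The test rule is generic, and a full analysis plan might refine it. However, the article does state an unadjusted method for continuous variables, so this is a comment on a stated choice and not on a missing detail.

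**Conclusion.** The point holds as one of efficiency and clarity for a secondary endpoint. The plan uses two unadjusted tests where one baseline-adjusted model would be more precise with the same data. The direction is safe for any plausible correlation. The size is not known: the variance ratios (1.19 to 2.78 for the discharge value, 1.43 to 1.11 for log change) rest on an assumed r of 0.4 to 0.8 and equal log variances. The gain of about 5 to 13 power points over the planned percent-change test further assumes lognormal data, a geometric mean ratio of 0.6 and a log SD of 1.0, and covers r from 0.5 to 0.8. Nothing here makes the planned tests invalid or touches the primary endpoint or the 29 per arm.

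**What to change.** Prespecify one NT-proBNP comparison. Regress log discharge NT-proBNP on arm, log admission NT-proBNP and the two stratification factors (age at 70 years, LVEF at 50%). Report the adjusted ratio of geometric means with its 95% CI. Name the pre-randomisation sample as the covariate, because the qualifying measurement and randomisation share the same 24-hour window after admission. Keep the raw discharge value and percent change as descriptive summaries without their own tests, and drop the normality-test rule for this endpoint.

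The change is to analysis wording only: no new patients, samples or visits. Five parameters leave 58 − 5 = 53 residual degrees of freedom, against 58 − 2 = 56 for a two-sample t-test, so the cost is three degrees of freedom.

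It does not solve two other matters: the discharge sample may be taken at different times after admission in the two arms, and missing discharge values will not be imputed.
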